## Abstract

**Background:**

Up to fifty percent of microbiologically cured tuberculosis (TB) patients may be left with permanent, moderate or severe pulmonary function impairment. Very few studies have systematically examined pulmonary outcomes in patients to understand the pathophysiologic basis and long-term socio-economic consequences of this injury. The planned multi-country, multi-centre observational TB cohort study, aims to advance the understanding of the clinical, microbiological, immunological and socio-economic risk factors affecting long-term outcome of pulmonary TB. It will also determine the occurrence of reversible and irreversible socio-economic consequences to patients, their households and the health sector related to pulmonary TB disease and its treatment.

**Methods:**

We will enrol up to 1.600 patients with drug sensitive and multidrug-resistant pulmonary TB who are treated according to the local standard of care by the respective National TB Program. Recruitment is taking place at the time of TB diagnosis at four African study clinics located in The Gambia, Mozambique, South Africa and Tanzania. The primary outcome is the proportion of TB patients with severe lung impairment measured by spirometry at 24 months after TB treatment initiation. Biological samples, including sputum, urine and blood, for studying host- and pathogenic risk factors will be collected longitudinally and examined in a nested case-control fashion. A standardized quality of life questionnaire will be used together with a novel version of WHO’s generic patient cost instrument which has been adapted for the longitudinal study design.

**Discussion:**

This study is an integral part of an overall strategy to fill a knowledge gap needed to improve TB treatment outcomes globally. The main scientific goal is to identify the major pathogenic mechanisms associated with poor TB treatment outcomes, so that such pathways can be interrupted to avert long term TB sequelae. National as well as supra-national stakeholders and decision makers have been integrated early in the study planning process to inform future treatment guidelines and national health policies.

**Trial registration:**

ClinicalTrials.gov: NCT03251196, August 16, 2017.

**Electronic supplementary material:**

The online version of this article (10.1186/s12890-018-0777-3) contains supplementary material, which is available to authorized users.

## Background

Tuberculosis (TB) remains one of the world’s deadliest communicable diseases. In 2016, an estimated 10.4 million people developed TB and 1.3 million died from the disease [1]. TB related morbidity and mortality remain particularly high in African countries, mainly due to the impact of HIV, sustained poverty and food insecurity as well as due to treatment challenges including the rise in drug-resistant TB [2].

For the past 40 years, treatment success in tuberculosis has been defined as the eradication of active infection whilst preventing resistance and recurrence, achieved through multidrug antimicrobial treatment. Current estimates of the global TB disease burden include incidence and prevalence of active TB, TB death rates, and disability-adjusted years of life (DALY) lost due to active TB, but do not consider DALYs lost due to long-term disability due to TB sequelae or reduced longevity in patients considered cured [3, 4]. However, accumulating evidence indicates that permanent lung injury due to TB is frequent and substantial. In one study in Papua New Guinea, the mean FEV1 (the maximal volume of air exhaled in the first second after a full inspiration), was reduced to 64% of that of healthy controls at the time of TB diagnosis [5]. FEV1 improved by 11% after 2 months of TB treatment, but did not further improve subsequently. At the conclusion of successful anti-microbial treatment, 27% of TB patients still had moderate or severe impairment of pulmonary function. [5]. Another study from India found severe and irreversible obstructive pulmonary ventilation defects in one-third of TB patients one year after completion of TB treatment [6]. A literature review of South African studies showed that lung function impairment and chest symptoms were consistently associated with pulmonary TB [7]. In the United States, studies demonstrated that even persons cured from TB have considerably shortened life expectancy [5, 6]. There is limited evidence on pulmonary function impairment in African populations outside South Africa and presently no estimates of the impact of TB on life expectancy in African patients. Further, associated risk factors contributing to permanent lung function impairment after TB are unknown.

### Clinical, environmental and behavioural risk factors

The risk of developing TB is up to 30 times greater in people living with HIV than among those without HIV infection [8]. TB patients with advanced AIDS are at increased risk of immune reconstitution inflammatory syndrome (IRIS) and death. The long-term effects of HIV and antiretroviral treatment on lung function, however, are not known. Diabetes mellitus is also recognized as a TB risk factor and the African region is experiencing an increasing prevalence of diabetes alongside other non-communicable diseases [9–11]. However, little is known about the potential impact of diabetes on long-term TB outcomes. Other risk factors that can potentially have long term effects include pre-existing pulmonary conditions like Chronic Obstructive Pulmonary Disease (COPD) and asthma, and associated risk factors such as smoking, indoor air pollution and harmful alcohol use [12, 13]. Malnutrition is also an important risk factor for TB [14], however, the association with sequelae after treatment has not been studied.

### Host-immune response and associated risk factors

It is well known that host responses to Mycobacterium tuberculosis (MTB) also contribute to lung pathology through excessive induction of the inflammatory pathway. However, whether the systemic host response before and after TB treatment initiation can be used to predict pathology and treatment outcomes is largely unknown. Blood and sputum-derived neutrophil activation and inflammatory mediators will be examined in order to elucidate the predominant pathway of lung inflammation in TB and inform on future host-adjunctive therapy strategies. For example, polymorpho-nuclear neutrophilic granulocytes have been associated with active tuberculosis and the failure to control the infection, and likely contribute to exacerbated pathology and long term sequelae and lung function loss [15–17]. Additionally, there are very few studies that have assessed specific host biomarkers in clinical research studies, such as the T-cell activation marker-tuberculosis (TAM TB) assay [18], which have shown a correlation with diagnosis and treatment response in TB [19].

### Pathogen diversity and microbial risk factors

There is increasing evidence that genomic diversity of the MTB complex influences important patho-biological properties, such as transmissibility and pathogenicity, and affects host-immune responses and clinical manifestations [20, 21]. Moreover, microbial factors are recognized as important determinants of microbiologic outcomes such as treatment failure or relapse. Baseline drug resistance can affect the risk of new (acquired) resistance and subsequent treatment failure. For some drugs, such as rifampin, this effect can be profound [22]. Sputum bacillary burden at baseline and culture status after 2 months of treatment affect relapse risk [23]. However, very little is known about the contributions of all these and other microbial factors, such as strain genetic background or the presence of mixed infections, on long-term pulmonary function outcomes.

### Socio-economic determinants and costs of tuberculosis

Several previous studies have documented high patient costs before patients are diagnosed and during TB treatment [24, 25], where patients may lose about half of their household income due to TB. Loss of income and direct expenses may result in poorer treatment outcomes, including increased risk of TB infection and progression, the development of drug resistance and long term pulmonary impairment. The WHO End TB Strategy has included an microeconomic target, that no TB patient or affected household should experience catastrophic expenditure or costs related to TB illness and TB care [26], and a generic protocol for the measurement of catastrophic costs due to TB has been developed [27]. Measuring catastrophic cost is a useful indicator of equality in advancing towards universal health coverage. Although patient costs during diagnosis and TB treatment has been documented there is little evidence on the costs and socioeconomic consequences of TB after treatment has been completed and how they are associated to different clinical TB outcomes. In addition, the published literature contains surprisingly little evidence about the costs to the health systems of treating TB and TB sequelae, especially in Africa.

### Study aim

TB Sequel project aims to: i) advance understanding of the clinical, microbiological, immunological and socio-economic risk factors affecting or predicting the long-term pulmonary function outcome; ii) determine costs on patient and health system level related to TB disease, TB treatment and TB sequelae.

## Methods/design

### Study partners and setting

The TB Sequel cohort study is conducted by the TB Sequel consortium including a number of research institutions based in Africa and Europe (Additional file 1). The Division of Infectious Diseases and Tropical Medicine at the University of Munich (LMU), Germany and The AURUM Institute in Johannesburg, South Africa coordinate the project. The TB Sequel cohort study will recruit TB patients in four African countries of which three belong to high TB burden countries. In Johannesburg, South Africa, the study is conducted by the University of Witwatersrand (WITS) at the Clinical HIV Research Unit (CHRU) located at the Helen Joseph Hospital that serves an urban area with approximately one million inhabitants. In Mbeya, Tanzania, the study takes place at the National Institute of Medical Research - Mbeya Medical Research Centre (NIMR-MMRC). The NIMR-MMRC is located within the same premises of the Mbeya Zonal Referral Hospital (MZRH), one of the four largest referral hospitals in Tanzania, which serves a total population of about 500.000 inhabitants. In Maputo, Mozambique, the Instituto Nacional de Saúde (INS) is conducting the TB Sequel cohort study at two research units, first located in Mavalane Health Centre (City of Maputo) serving approximately 620.000 inhabitants, and second, located in Machava General Hospital (Province of Maputo) where the majority of MDR-TB patients of Maputo are treated. In The Gambia, this study is conducted by the Medical Research Council (MRC) Unit The Gambia in the Greater Banjul area, where two thirds of all TB patients diagnosed in the country present. The Research Center Borstel (FZB) in Germany is responsible for MTB isolates typing and contributes to host responses studies including training of African researchers. The socio-economic sub-study is being led by the Health Economics and Epidemiology Research Office (HE^2^RO) at WITS University in South Africa in collaboration with the Department of Public Health Sciences at Karolinska Institutet, Sweden and WHO Geneva.

### Study design

We will conduct a prospective, multi-country, multi-centre, observational cohort study and recruit up to 1.600 pulmonary TB patients at the time of TB diagnosis who will be followed during and after TB treatment. At enrolment, TB diagnosis is based on sputum tested positive for the presence of MTB either by Xpert MTB/RIF (or Ultra) or culture methods (Fig. 1). At baseline and at defined study visits (see Schedule of Events (SOE) Table 1) clinical data, data on risk factors, information on comorbidities, socio-economic data, as well as biological samples (sputum, urine and blood) will be collected from all participants. This large cohort will therefore serve as a platform for all nested research activities related to immunological, microbiological and socio-economic studies as well as future therapeutic interventions (Additional file 2).

**Fig. 1 Fig1:**
[figure not shown]
Screening algorithm

**Table 1 Tab1:** Schedule of Events (SOE)

Activities	Screening	Baseline	Day 14	Month 2	Month 4	Month 6	Month 9	Month 12	Month 18	Month 24
Visits										
Eligibility assessment	x									
Xpert MTB/RIF (Ultra) assay	x									
Sputum smear and culture	x	x		x	x	x	(x)	(x)	(x)	(x)
Drug sensitivity testing		x								
Demographic data		x								
Clinical examination		x	x	x	x	x	x	x	x	x
Chest X-ray		x				x				x
Lung function assessment		x		x		x	x	x	x	x
ECG		x						x		x
Medical history (update)		x	x	x	x	x	x	x	x	x
TB treatment and adherence			x	x	x	x	(x)	(x)	(x)	(x)
Quality of life/patient’s cost questionnaire		x		x		x		x		x
HIV test (CD4 count)		x						x		x
Hepatitis B serology		x								
Haematology and Biochemistry		x				x		x		x
Urine dip stick test		x		x	x	x				
Blood storage for nested research studies		x	x	x	x	x	x	x		
Sputum storage for nested research studies		x	x	x	x	x	(x)	(x)	(x)	(x)
Urine storage for nested research studies		x		x	x	x	(x)	(x)	(x)	(x)

### Participant eligibility

For enrolment, each study participant must meet all of the inclusion criteria and none of the exclusion criteria summarized in Table 2.

**Table 2 Tab2:** Inclusion and exclusion criteria

	Inclusion criteria	Exclusion criteria
1	At least one sputum sample tested positive for MTB by Xpert MTB/RIF assay in the study clinic/study laboratory or at least one sputum sample tested positive by culture methods in study laboratory or other TB laboratory	Anti-TB treatment in the last 6 months^a^
2	Be ≥18 years of age	Incapacity to produce and provide two sputum samples of sufficient volume and quality^b^
3	Willing to provide a written consent or witnessed oral consent in the case of illiteracy for participation in the study, prior to patient’s first sample or other study-specific data being collected	Severe medical or psychiatric condition which in the opinion of the site investigator or designee, might interfere with the ability to give true informed consent and to adhere to the study requirements
4	Willing to be tested for HIV infection	Currently imprisoned
5	Agreeing to the collection and storage of blood, urine, and sputum specimens	Taking part in investigational product trials related to TB and/or lung diseases
6	Willing to start anti-TB treatment after TB diagnosis	
7	Living within the study area and willing to inform the study team of any change of address during the treatment and follow up period	

^a^To ensure that no treatment failure are recruited into (immunological or genetic) marker studies

^b^To ensure sufficient amount of sputum for host- and mycobacterial marker studies

### Duration of study

Recruitment commenced in September 2017 and is expected to continue until September 2019. Follow-up will last for a minimum of 24 months in all participants to ensure that any loss in reported lung function will have become chronic during follow-up [28]. Further, the chronicity and final degree of long term costs and comorbidities resulting from TB disease or treatment shall be confirmed by a follow up period of at least 24 months length. End of study is expected in September 2021.

### Primary outcome and study endpoints

The primary outcome is a proportion of TB patients with severe pulmonary function impairment (restrictive, obstructive or mixed ventilation impairment), measured by spirometry at 24 months from TB treatment initiation and compared to national reference values. Long term lung function impairment is considered a clinically meaningful condition contributing to long term morbidity and mortality in former TB patients.

Amongst secondary outcomes are: the proportion of subjects with any impairment of pulmonary function as well as severity and type of impairment at TB diagnosis and 2, 6, 12 and 18 months; proportion of subjects with liquid and solid MTB culture conversion at different time points during or at the end of anti-TB treatment; the frequency of all-cause hospitalization episodes and all-cause mortality during follow-up of 24 months; the proportion of subjects with recurrent TB and; the proportion of subjects suffering from ongoing non-pulmonary comorbidities which are related to TB disease and treatment at different time points during 24 months of follow-up.

Studies regarding host immunology- and pathogen-associated risk factors and markers are planned as explorative, nested, case-control studies. Sample selection will be based on specific outcomes and risk factors present in the study participants.

Main outcomes studied in the context of socio-economic research are the proportion of subjects incurring catastrophic cost due to TB by the end of treatment; changes in income within follow up period; and scales for quality of life and general disability at treatment start, end of treatment and at follow-up. The cost of providing TB care and treatment, will be estimated from the health provider perspective, for both drug sensitive and drug resistant TB.

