### Sample size

We hypothesized that the prevalence of the primary endpoint - severe lung impairment at 24 months period of follow up after TB diagnosis (conservative estimation based on a literature review) will be 15%. A sample size of 1.600 patients allows the estimation of the primary end point in the total cohort with a precision (half width of the 95% confidence interval) of about 1.75%. In addition, the prevalence within specific subgroups can be estimated adequately, e.g. with a precision between 2.5 and 7.8% in subgroups with a proportion of 50% (e.g. HIV) and 5% (e.g. diabetes) of the total cohort, respectively. Moreover, based on a pre-set alpha of 5% (two-sided) the sample size allows the detection of risk factors causing a duplication of the prevalence of severe lung impairment with a power of at least 80%, even for risk factors with a low prevalence of 5% in the total cohort. Depending on the availability and quality of patient’s end-point data, or if the prevalence of the primary outcome is less than 15%, it may be necessary to recruit more or less participants into the study.

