The present lack of knowledge regarding the pathogenic mechanisms or clinical co-factors causing adverse outcomes in TB hinders the development and evaluation of interventions to reduce the overall TB disease burden or costs related to TB. Additionally, the lack of current, geographically relevant information about the economic impact of TB and the likely costs to national health systems pose an obstacle to efficient resource allocation both within TB programs and across competing health and social care priorities. Studies, such as TB Sequel, examining long term disability and associated risk factors, income loss, and treatment-related costs are crucial to inform the policy changes needed to address poor long-term TB outcome and catastrophic costs burden. Compared to other TB cohort studies TB Sequel will follow patients for at least 24 months which enables us to report lung outcome when any impairment related to TB disease has stabilized, thus when it can be assumed to have become chronic. Likewise the characteristics of ongoing socio-economic consequences and disease burden can be studied in those patients with relevant chronic lung or other TB related injury for at least 24 months. This allows for new estimates of TB disease burden which go beyond microbiological cure. Due to sample size and selection of different study sites across Africa we will be able to describe the influence of important potential risk factors on lung outcome such as infection with an MDR-TB strain, HIV-coinfection and comorbidities like COPD and diabetes but also the relevance of different genetic and socio-economic background. On the other hand, the follow-up of only 24 months precludes the investigation of interrelation of pulmonary TB with pre-existing and especially newly developed comorbidities as well as the influence of TB on long term survival and socio-economic status. Another limitation of the study is that the investigators have no influence on the composition of and adherence to anti-TB (and anti-retroviral) treatment and individual treatment regimens might have a different influence on lung outcome. On each study visit, co-medication and drug adherence are documented in order to enable sub-group analyses as well as to control for it during analysis of other risk factors for poor treatment outcomes. Finally, the capacities for adequate treatment and follow up for the majority of diagnosed comorbidities are currently limited or even not available at most study settings.

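### Month 24 from treatment start does not secure chronic impairment for participants still on, or recently off, TB treatment, so the MDR-TB contrast at that visit should not be read as a difference in permanent damage

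*Protocol article*

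**What the plan says.** The abstract (Methods) describes one cohort of patients with "drug sensitive and multidrug-resistant pulmonary TB who are treated according to the local standard of care". Under Primary outcome and study endpoints, severe impairment is "measured by spirometry at 24 months from TB treatment initiation and compared to national reference values". The Sample size section words the time point as "severe lung impairment at 24 months period of follow up after TB diagnosis". Neither wording refers to the end of treatment.

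Duration of study gives the reason for following all participants for at least 24 months: "to ensure that any loss in reported lung function will have become chronic during follow-up". The Discussion repeats the idea, saying of this follow-up: "which enables us to report lung outcome when any impairment related to TB disease has stabilized". Neither statement separates patients by length of treatment. The Discussion then says "we will be able to describe the influence of important potential risk factors on lung outcome such as infection with an MDR-TB strain", followed by HIV, COPD and diabetes.

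In Table 1 (Schedule of Events), the row "TB treatment and adherence" carries an unconditional mark from day 14 to month 6 and a bracketed mark at months 9, 12, 18 and 24. Lung function is scheduled at baseline and at months 2, 6, 9, 12, 18 and 24.

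**The concern.** Chronic impairment is a statement about a state that has settled once disease and treatment are over. The clock used here starts when treatment starts, and treatment length is left to national guidelines (Study procedures). If regimens differ in length, participants reach month 24 after unequal time off treatment, and a person still being treated has had none. The schedule itself leaves room for such people at the primary visit, while the chronicity statement is made for everyone.

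Two conclusions are exposed. The pooled proportion may be reported as chronic sequelae although it includes some impairment measured during or shortly after treatment. And an excess of severe impairment in MDR-TB may be taken as more lasting damage when part of it could be less time to recover. MDR-TB is not incidental to the cohort: one of the two Maputo research units is in the hospital where most of that city's MDR-TB patients are treated (Study partners and setting).

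**Working it through.** **1. The plan's own figures.** With an assumed prevalence of 15%, the half width of the 95% interval is 1.96 × √(0.15 × 0.85 / n).

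- n = 1,600: 1.75% (stated: about 1.75%)
- n = 800: 2.47% (stated: 2.5%)
- n = 80: 7.82% (stated: 7.8%)

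Power to detect 30% against 15% with 80 and 1,520 patients is 90.5%, or 86.3% in the least favourable variant tried (overall prevalence held at 15%, continuity correction). Both agree with the stated minimum of 80%. None of these figures is in dispute.

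**2. Time off treatment at the primary visit.** Time off = 24 − treatment duration. The durations below are assumptions; the protocol gives none. The last column places the scheduled spirometry visits on the same scale (visit month − duration).

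| Assumed course (months) | Time off at month 24 (months) | Scheduled spirometry at or after end of course, in months off treatment |
|---|---|---|
| 6 | 18 | 0, 3, 6, 12, 18 |
| 9 | 15 | 0, 3, 9, 15 |
| 12 | 12 | 0, 6, 12 |
| 18 | 6 | 0, 6 |
| 20 | 4 | 4 |
| 24 | 0 | 0 |

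Against a 6-month course, the gap at month 24 runs from 18 − 15 = 3 months to 18 − 0 = 18 months. After the longest courses, only one or two readings fall at or after the end of treatment, too few to show stability in those participants. Comparable readings do exist: month 24 after an 18-month course and month 12 after a 6-month course are both 6 months off treatment.

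**3. What a difference due to time off treatment alone could do.** Neither the MDR-TB share nor any effect of time off treatment is in the protocol, so this only illustrates scale. Suppose shorter time off treatment alone added 5, 10 or 15 points to a 15% prevalence in MDR-TB. The chance that a two-sided 5% test of MDR-TB against drug-sensitive TB (total 1,600) is significant would be:

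| Assumed MDR-TB share | +5 points | +10 points | +15 points |
|---|---|---|---|
| 5% | 25% | 65% | 90% |
| 10% | 39% | 87% | 99% |
| 20% | 58% | 98% | above 99% |

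The whole-cohort prevalence rises by share × added points: from 0.05 × 5 = 0.25 to 0.20 × 15 = 3 points. What is at stake is therefore mainly the reading of the MDR-TB contrast, and much less the pooled proportion.

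**4. Room in the timetable.** Recruitment runs to September 2019 and the study ends in September 2021, exactly 24 months later. The last recruits cannot be given a later visit counted from the end of treatment, so any remedy has to use the scheduled visits.

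**The case against.** A reader might go further and infer that MDR-TB patients are much closer to treatment than the others, or still on it, at month 24, and that the MDR-TB contrast is confounded by time off treatment. The documents do not support that.

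- **Durations.** No treatment length is given. At the short end of the assumed range the gap is only 3 months.
- **The bracketed marks.** Table 1 shows no legend for them, and the same marks appear at months 9 to 24 for smear and culture and for sputum and urine storage. They may refer to re-treatment for recurrence, which is a secondary outcome. They show that treatment at month 24 is provided for, not that it is expected in MDR-TB. Re-treatment is still active treatment, however, so the point about chronicity stands either way.
- **Confounding.** A longer regimen follows from having MDR-TB, so time off treatment lies on the pathway and is not a common cause. A contrast at a fixed time from treatment start is a coherent total effect.
- **Chronicity.** The claim is not refuted. The Background cites one study in which mean FEV1 stopped improving after 2 months of treatment, and Duration of study cites a reference that is not at hand. But the first is a group mean, reported without a breakdown by resistance, and does not establish stable severe impairment after long regimens.
- **Existing mitigation.** The Discussion concedes that regimens may affect lung outcome and foresees control for co-medication and adherence. Neither measures time since the end of treatment.
- **Level of detail.** The article is a condensed text and calls the analysis exploratory; an analysis by time off treatment may stand in the full protocol or SAP. That is fair for the analysis. The outcome clock and the unqualified chronicity statements, however, are fixed in the article itself.

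**Conclusion.** The point holds in a limited form. The article asserts chronicity for all participants on a clock that ignores the end of treatment, while its own schedule allows for treatment up to the primary visit. For anyone on treatment at month 24, or only recently off it, the statement is not secured. The MDR-TB contrast at month 24 remains valid as a total effect; the error would lie in reading it as a difference in permanent damage.

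The size of the problem rests on assumed durations and cannot be fixed from the document. The number of participants affected is unknown, and no bias in the primary proportion has been demonstrated. The inconsistency is worth correcting because it changes what may be concluded about MDR-TB and lasting damage, and the correction is cheap.

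**What to change.** 1. Keep the 24-month outcome and the fixed-time MDR-TB contrast, and describe the latter as a total effect at 24 months from treatment start.
2. In Duration of study, the Discussion and the eventual report, limit the word chronic to participants off TB treatment at month 24. Report treatment status at that visit and time since end of treatment, which requires the treatment end date to be captured.
3. Present the 24-month proportion separately for drug-sensitive and MDR-TB.
4. Add, as a sensitivity analysis only, an MDR-TB comparison at similar time since end of treatment, using the spirometry already scheduled at months 6, 9, 12, 18 and 24.

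The cost is a change of wording, one date per participant if it is not already recorded, and one secondary analysis; no visit is added. There are two downsides. Few MDR-TB readings will fall late after treatment. The matched comparison also conditions on having completed treatment, so it drops those who die, fail or are lost before then, possibly unequally between the groups, and it compares groups at unequal time since diagnosis. These limits should be stated with the result, and the analysis should not replace the fixed-time contrast.
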